### 4.6 Tumor Response

Assessed according to RECIST version 1.1 at 3 months post-RT completion, with classifications of Complete Response (CR), Partial Response (PR), Stable Disease (SD), and Progressive Disease (PD).

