## 2. Objectives of the research

- **Primary Objectives:** To investigate the effect of SHINE-MDT on the rate of radiotherapy interruption.
- **Secondary objective:** To evaluate patients' QoL, nutritional status, psychological well-being, rehospitalization rate, and tumor response.
  - To investigate the impact of SHINE-MDT on patients' QoL based on the European Organization for Research and Treatment of Cancer (EORTC) Quality-of-life Questionnaire Core 30 (EORTC QLQ-C30) and Head and Neck Cancer Module (EORTC QLQ-H&N35).
  - To investigate the effect of SHINE-MDT on patients' nutritional status based on the Nutritional Risk Screening 2002 (NRS 2002) and PG-SGA.
  - To investigate the impact of SHINE-MDT care on patients' psychological status based on the Distress Thermometer (DT), Patient Health Questionnaire-9 (PHQ-9), and Hospital Anxiety and Depression Scale (HADS)
  - To investigate the impact of SHINE-MDT on the rehospitalization rate.
  - To investigate the effect of SHINE-MDT on tumor response according to RECIST version 1.1.

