## 3. Study design, methods and procedures

### 3.1 Study design

A two-arm, randomized, single-center, prospective study.

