### 3.2 Methods and Procedures

#### ➤ **Patients Enrollment:**

- Inclusion criteria:

1. Male or female patients:  $\geq 18$  years;
2. Expected survival  $\geq 6$  months;
3. Pathologically confirmed malignant head and neck tumors (including nasopharyngeal carcinoma) without distant metastasis;
4. Scheduled to undergo definitive radiotherapy or postoperative adjuvant radiotherapy;
5. Systemic functional status Eastern Cooperative Oncology Group (ECOG) (Appendix 2) rating  $\leq 2$ ;
6. Adequate cognitive and reading abilities to complete the questionnaire;
7. Sign the informed consent.

- Exclusion criteria:

1. Other malignant tumors aside from head and neck malignancies (excluding treated basal cell carcinoma of the skin or in situ cervical cancer);
2. History of prior head and neck radiotherapy;
3. History of mental disorders diagnosed by a psychiatrist according to ICD-10 criteria, or history of psychotropic medication use;
4. Absolute contraindications for head and neck radiotherapy;
5. Uncontrolled systemic diseases that significantly impact the quality of life, such as poorly controlled diabetes, heart failure (NYHA classification III-IV; Appendix 4), or interstitial lung disease;

- Withdrawal Criteria:

Withdrawal criteria include, but are not limited to:

1. Patients who cancel their informed consent;
2. Patients who are non-compliant with the study protocol;

3. Patients assessed by researchers as unsuitable to continue.

➤ **Randomization and Blinding**

All patients were randomly assigned in a 1:1 ratio to one of two groups: the UC group or the SHINE-MDT group. The randomization process was done using a computer-generated random assignment list based on a randomized permutation block design.

Group allocation was performed using block randomization, with eligible patients being randomly assigned in a 1:1 ratio to either the UC group or the SHINE-MDT group. The statisticians designed the block size, assignment order list, and random numbers, with an equal number of patients in the UC and SHINE-MDT groups within each block. Only the statistical design personnel knew the block size (variable block size of 4 or 6). Concealment was achieved using opaque, sealed envelopes. The statistical design personnel prepared sealed envelopes with random group assignments for each participant. Sequentially, the envelopes were opened upon participant enrollment, determining the group assignment according to the allocation disclosed within the envelope.

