### 3.3 Contamination Control

- Spatial Segregation

The UC cohort received standard therapy (including radiotherapy) in the First Inpatient Department, while the SHINE-MDT cohort underwent identical protocols within a physically separated Medical Technology Building.

- Temporal Isolation

Treatment sessions for the MDT cohort were scheduled exclusively in morning blocks (08:00–13:00), with UC cohort sessions allocated to afternoon blocks (14:00–18:00). This eliminated unstructured patient interactions in shared waiting areas.

- Care Team Separation

MDT specialists (nutritional, psychological, and rehabilitation) were exclusively assigned to the intervention cohort and were not involved in UC cohort management.

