a If a CR is truly met at the first time point, then any disease seen at a subsequent time point, even a disease meeting PR criteria relative to baseline, makes the disease PD at that point (since the disease must have reappeared after CR). The best response would depend on whether the minimum duration for SD was met. However, sometimes 'CR' may be claimed when subsequent scans suggest small lesions were likely still present and, in fact, the patient had PR, not CR, at the first time point. Under these circumstances, the original CR should be changed to PR, and the best response should be PR.

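### The section announcing blinding covers only allocation and concealment, and section 4.6 sets no masked scan reading, so the 3-month RECIST response can be judged with the arm known

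*Protocol*

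**What the plan says.** Section 3.1 describes the trial as "A two-arm, randomized, single-center, prospective study", with no term for masking. The part of section 3.2 headed "Randomization and Blinding" covers sequence generation, block size and concealment: "Only the statistical design personnel knew the block size (variable block size of 4 or 6" and "Concealment was achieved using opaque, sealed envelopes". It names no patient, clinician, assessor, scan reader or analyst as masked, and does not call the trial open-label.

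Section 2 lists as a secondary objective "To investigate the effect of SHINE-MDT on tumor response according to RECIST version 1.1". Section 4.6 fixes the criteria, the time and the four response categories ("Assessed according to RECIST version 1.1 at 3 months post-RT completion"). It names no reader and sets no masking. Appendix 3 restates RECIST and asks for consistent imaging, again with nothing on masked or independent reading.

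Two other places bear on who knows the arm. Section 3.2 (Intervention Strategies) puts radiation and medical oncologists in the SHINE-MDT team. Section 3.3 has the usual-care patients treated in the First Inpatient Department and the SHINE-MDT patients "within a physically separated Medical Technology Building", in separate halves of the day.

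**The concern.** Supportive care of this kind cannot be hidden from patients or from those who give it, but a scan can be read without knowing the arm. The protocol opens a section on blinding and then deals only with allocation. Concealment protects the assignment; it does nothing for an outcome judged months later.

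Tumour response is the only tumour outcome among the objectives, and the Background argues that interruption undermines tumour control. A difference in complete response would be read as support for that argument. If the reader knew the arm, the difference could not be separated from the reader's expectation.

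**Working it through.** **Step 1: is anyone masked?** Section 3.1, the randomisation text in 3.2, section 4.6 and Appendix 3, taken together, withhold only the block size and the next assignment. Both matter before allocation, and neither masks anyone afterwards.

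**Step 2: who knows the arm?** Treating staff do. Oncologists belong to the SHINE-MDT team, and the arms are separated by building and time of day. Nothing in 4.6 prevents one of these clinicians from making the response call.

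**Step 3: where does judgement enter the CR call?** Under Appendix 3 (item 5 and Table 3-1), overall CR needs all target lesions gone, non-target disease in CR, no new lesions, and pathological nodes below 10 mm in short axis. The judgement that can move a patient between CR and PR is therefore whether residual or non-target disease is present, and the nodal short axis.

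**Step 4: illustration of size.** The protocol gives no response rate, so there is no figure of its own to reproduce on this point. All response and upgrading inputs are assumptions:

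- evaluable patients per arm, n: 100 (close to 107 × 0.95 = 101.65, from the size and dropout in section 6.1), and 50, because postoperative patients are eligible and some may have no lesion to assess;
- true CR rate, c: 50%, 60% or 70%, the same in both arms;
- CR plus PR: 90%, so PR = 0.9 − c;
- share of PR called CR in one arm only, u: 0, 10%, 20% or 30%.

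The observed CR rate is c in one arm and c + u(0.9 − c) in the other, so the spurious difference is u(0.9 − c). Example: c = 0.5 and u = 0.2 give 0.2 × 0.4 = 0.08, or 8 points.

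The test is z = (p₂ − p₁) / √(2p̄(1 − p̄)/n), where p₁ and p₂ are the observed CR proportions and p̄ is their mean, rejecting when |z| > 1.96. The rejection probability is the sum of exact binomial probabilities over all pairs of counts that reject.

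| True CR | u | Spurious difference (points) | Rejects, n = 100 | Rejects, n = 50 |
|---|---|---|---|---|
| 50% | 0 | 0 | 5.6% | 5.7% |
| 50% | 10% | 4 | 9.6% | 7.7% |
| 50% | 20% | 8 | 21.8% | 13.7% |
| 50% | 30% | 12 | 41.6% | 24.0% |
| 60% | 0 | 0 | 5.1% | 5.2% |
| 60% | 10% | 3 | 7.3% | 6.2% |
| 60% | 20% | 6 | 14.2% | 9.5% |
| 60% | 30% | 9 | 26.4% | 15.4% |
| 70% | 0 | 0 | 5.1% | 5.0% |
| 70% | 10% | 2 | 6.2% | 5.6% |
| 70% | 20% | 4 | 9.7% | 7.3% |
| 70% | 30% | 6 | 15.8% | 10.4% |

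With 10% upgrading the excess over the nominal 5% is small. It becomes material at 20-30%, most of all when the true CR rate is low and so more patients are in PR.

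**The case against.** The best reply is that the protocol is silent rather than wrong. It names no reader, so it does not say that the reader knows the arm, and hospital radiologists may in practice have read the scans without knowing it. The endpoint is secondary, and upgrading in one arm only is a worst case. All of this stands, and it limits the point to a risk. It does not remove it: who reads a scan, and with what information, is trial conduct that belongs in the protocol, so an unseen SAP would not normally settle it.

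A reader might infer more than the documents support:

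- *That the imaging request gives away the arm.* Section 3.3 separates where therapy is given. It does not say who orders the 3-month scan, where it is done or what the request shows.
- *That Appendix 3 concedes CR is over-called here.* The remark that CR "may be claimed when subsequent scans suggest small lesions were likely still present" is in a footnote to Table 3-3, on best overall response when confirmation is required. It depends on later scans and says nothing about knowledge of the arm. Section 4.6 uses a single time point, so that table does not govern it.
- *That choosing up to five target lesions, or the longest axis, drives the error.* A residual lesion blocks CR whether it is target or non-target. Appendix 3 also already requires target lesions to be defined at baseline.
- *That this is the only endpoint tied to the trial's rationale.* The Background links interruption itself, the primary endpoint, to tumour control.

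**Conclusion.** The point holds as a risk of bias in one secondary endpoint. As written, the protocol allows the 3-month response to be judged by someone who knows the arm, although masked reading is feasible.

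Under the stated assumptions, the spurious CR difference is 2-12 points. The chance of a significant result with no true difference is 6-42% with 100 evaluable per arm and 6-24% with 50, against about 5-6% without bias. The documents support no particular amount or direction of upgrading, so these figures show what is possible and do not estimate what happened. The change is worth making because it is cheap. The primary endpoint is a count of days against the planned schedule; neither it nor the sample size of 214 is affected.

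**What to change.** In section 4.6, state that whoever already reads the baseline and 3-month scans does so on coded scans, without arm, treatment location or clinic notes, and that this masked reading is the one analysed. Tumour site and postoperative status may be shown. If treating oncologists would otherwise make the call, use the routine radiology reading with the arm withheld. This adds no reader, provided that such a reading exists, which the protocol does not say.

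Under the blinding heading in section 3.2, state that patients and care staff are not masked and that tumour response is read masked.

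If scans have already been read with the arm known, stored scans can be re-read in the same way, with agreement between the two readings reported.

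The cost is some handling work to code the scans, a short addition to the text, and less clinical context for the reader. No extra scan or patient is needed.

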## 5. Adverse Events and Serious Adverse Events

### 5.1 Adverse Events (AE)

An AE is an adverse medical event that occurs in clinical study subjects after receiving treatment but is not necessarily causally related to the treatment. Adverse events also include pre-existing diseases that increase in frequency and severity during the study.

➤ **AEs do not encompass the following situations:**

1. Conditions, diseases, or laboratory test abnormalities pre-exist or are detected before screening and do not further deteriorate.
2. Instances where adverse medical events did not occur (such as hospitalization due to elective surgery, social reasons, and/or personal convenience)

➤ **Expected Adverse Events of the Study:**

The expected adverse events in this study primarily involve those associated with radiotherapy and chemotherapy for head and neck tumors. The severity of acute radiotherapy reactions and chemotherapy-related adverse events will be evaluated using the RTOG acute radiation morbidity scoring criteria, RTOG/EORTC late radiation morbidity scoring scheme, and the NCI CTCAE Version 5.0.

## 5.2 Serious Adverse Events

A serious adverse event (SAE) is an adverse event that meets any of the following criteria:

1. Causing death;
2. Life-threatening;
3. Requires hospitalization or extended hospitalization;
4. Causing permanent or severe disability/incapacity;
5. Causing congenital anomalies/congenital disabilities;
6. Other significant medical events.

Significant medical events that cannot result in death, life-threatening situations, or hospitalization can also be considered SAEs related to the treatment if they may harm the subject. Based on appropriate medical diagnosis, medical or surgical intervention should be provided to prevent any of the outcomes defined above.

### 5.3 Classification of Adverse Events

The investigators will grade the severity of each AE according to the RTOG acute radiation morbidity scoring criteria, RTOG/EORTC late radiation morbidity scoring scheme, and the NCI CTCAE Version 5.0. If the severity of an AE is not specified in the guidelines, the investigator may assess it based on a general definition of grades 1 to 5 combined with medical judgment. The general grading of AEs is as follows:

Grade 1: Mild; asymptomatic or mild; seen only clinically or diagnostically; no treatment required.

Grade 2: Moderate; requiring minor, local, or non-invasive treatment; limitations in instrumental activities of daily living equivalent to age\*.

Grade 3: Severe or medically significant but not immediately life-threatening; causing hospitalization or prolonged hospitalization; causing disability; limitations in activities of daily living\*\*.

Grade 4: Life-threatening; requires urgent treatment.

Grade 5: Death related to AE.

\* Instrumental activities of daily living include cooking, buying clothes, using the telephone, managing money, and other related activities.

\*\* Personal activities of daily living refer to bathing, dressing, undressing, eating, grooming, medication use, etc., but do not include being bedridden.

## 5.4 Relevance judgment

eTable2: Adverse Drug Reaction Causality Assessment Form

| Criteria                              | Definitely Related | Possibly Related | Possibly Unrelated | Definitely Unrelated | Unable to Determine |
|---------------------------------------|--------------------|------------------|--------------------|----------------------|---------------------|
| Reasonable Temporal Sequence          | Yes                | Yes              | Yes                | Yes                  | Yes                 |
| Known Treatment Reaction Type         | Yes                | Yes              | No                 | No                   | Yes/No/Unknown      |
| An improvement upon Causative Removal | Yes                | Yes/No           | Yes/No             | No                   | Yes/No/Unknown      |
| Recurrence upon Re-administration     | Yes                | Unknown          | Unknown            | No                   | Yes/No/Unknown      |
| Alternative Explanations Possible     | No                 | Yes/No           | Yes/No             | Yes                  | Yes/No/Unknown      |

## 6. Statistical Analysis

### 6.1 Determination of Sample Size

Based on literature reports and clinical experience, the radiotherapy interruption in the control group is approximately 25%, while it was expected to be 10% in the experimental group. With a significance level ( $\alpha$ ) set at 0.025 (one-sided) and a power ( $1-\beta$ ) of 0.8, an overall predicted dropout rate of 5%, and a required sample size of 214 participants, with each group consisting of 107 participants.

### 6.2 Statistical Analysis Population

#### ➤ ITT (Intention-to-Treat) Set:

This includes all randomized participants in the treatment groups, regardless of whether they completed the treatment or adhered to the protocol. The analysis is based on the initial group assignment to reflect real-world scenarios.

➤ **FAS (Full Analysis Set):**

This includes all participants who received the study intervention (questionnaire assessments and radiotherapy). The analysis was conducted according to the initial randomization group but may account for deviations from the protocol.

➤ **PPS (Per-Protocol Set):**

This includes only those participants who completed the study according to the protocol. The analysis strictly follows the randomized groups and is typically used to assess the treatment effect under ideal conditions.

## **Appendix 1: National Cancer Institute Common Terminology Criteria for Adverse Events (NCI CTCAE) version 5.0**

For comprehensive details, please refer to the complete standard available at NCI CTCAE v5.0 or access the online information at the following NCI website:  
[https://ctep.canCE-r.gov/protocolDevelopment/electronic\\_applications/ctc.htm](https://ctep.canCE-r.gov/protocolDevelopment/electronic_applications/ctc.htm).

## Appendix 2: Eastern Cooperative Oncology Group (ECOG) - Performance Status Conversion

| Score | Description                                                                                                                       |
|-------|-----------------------------------------------------------------------------------------------------------------------------------|
| 0     | Fully active, able to carry on all pre-disease performances without restriction.                                                  |
| 1     | Restricted in physically strenuous activity but ambulatory and able to carry out work of a light or sedentary nature, office work |
| 2     | Ambulatory and capable of all self-care but unable to carry out any work activities; Up and about more than 50% of waking hours   |
| 3     | Capable of only limited self-care, confined to bed or chair for more than 50% of waking hours                                     |
| 4     | Completely disabled; Cannot carry on any self-care; Totally confined to bed or chair                                              |
| 5     | Death                                                                                                                             |

### Appendix 3: Response Evaluation Criteria In Solid Tumours - RECIST 1.1

Note: The radiographic efficacy evaluation in this study follows the RECIST 1.1 criteria. For detailed criteria, please refer to the references: *Eisenhauer EA, Therasse P, Bogaerts J, et al. New response evaluation criteria in solid tumors: revised RECIST guideline (version 1.1). Eur. J. Cancer. 2009;45(2):228–247.*

This protocol only presents the main principles of RECIST 1.1:

- 1) A baseline scan is performed not more than one month before the start of treatment. The subsequent response to treatment is evaluated against this scan or the subsequent scan demonstrating the lowest sum of the target disease (nadir).
- 2) Target lesions are defined at baseline and must be  $\geq 10$  mm in longest diameter or  $\geq 15$  mm in the short axis if the lesion is a lymph node (although lymph nodes  $\geq 10$  mm are considered pathological but non-measurable). If the CT slice thickness is  $> 5$  mm, the extranodal disease must be  $\geq$  twice the slice thickness. Measurable disease on a chest radiograph is  $\geq 20$  mm, provided the lesion is "clearly defined and surrounded by aerated lung."
- 3) A maximum of 5 lesions may be chosen, with a maximum of 2 per organ. The sum of all the extra-nodal long-axis measurements and nodal short-axis measurements is calculated. When analyzing a follow-up scan, the same lesions are measured, and the sum of the target disease is again calculated. Measurements need not be along the same axis (as measured at baseline) but should always be the longest axis of the lesion at that point in time. It does not even have to be at the same slice position, provided the measurement is of the same lesion. However, if the initial measurements are in the axial plane, all further measurements of that lesion must remain in the axial plane. Likewise, if the initial measurements are in the coronal plane (this is acceptable although not well defined in RECIST 1.1), all further measurements of that lesion must be in the coronal plane (assumed).
- 4) Bone lesions with a soft tissue component  $\geq 10$  mm can be designated as target lesions. Sclerotic bone lesions can not be used. Although solid lesions should be used in preference, cystic lesions may be used, provided they represent the disease being studied.
- 5) Evaluation of target lesions
  - ① Complete Response (CR): Disappearance of all target lesions. Any pathological lymph nodes (whether target or non-target) must have a reduction in the short axis to

<10 mm.

- ② Partial Response (PR): At least a 30% decrease in the sum of diameters of target lesions, taking as reference the baseline sum diameters.
  - ③ Progressive Disease (PD): At least a 20% increase in the sum of diameters of target lesions, taking as reference the smallest sum in the study (this includes the baseline sum if that is the smallest in the study). In addition to the relative increase of 20%, the sum must also demonstrate an absolute increase of at least 5 mm. (Note: the appearance of one or more new lesions is also considered progression).
  - ④ Stable Disease (SD): Neither sufficient shrinkage to qualify for PR nor sufficient increase to qualify for PD, taking as reference the smallest sum diameters while on study.
- 6) If a lesion reappears after disappearing in a patient with complete response, progressive disease is declared. However, if such a lesion behaves in this manner in a patient with stable disease or partial response, it is the change in sum of target disease that defines the response or progression.
- 7) PET-CT and MR may be used. The main specification is that imaging protocols are consistent throughout the trial. Therefore, contrast timings, MR sequences, and planes should remain the same.

